**Fig 1 pone.0348347.g001:**
[figure not shown]
SPIRIT schedule of enrolment, interventions, and assessments.

**Fig 2 pone.0348347.g002:**
[figure not shown]
CONSORT flow diagram of participant progression.

### Sample size calculation

The number of patients was determined using G*Power (version 3.1.9.7) based on changes in neuropathic pain scores from a study by [29], which examined the effect of the Michigan Diabetic Neuropathy Score (MDNS), a validated tool used to assess the severity of diabetic peripheral neuropathy. 42 subjects per group were shown to be necessary based on an effect size of 0.62, an alpha level of 0.05, and a power of 0.8. Hence, the total sample size was 84. [30]. We anticipate a 10% dropout rate, so we will recruit 90 participants in total and allocate them equally between the two groups.

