### Data analysis

All statistical analyses will be performed using appropriate statistical software (SPSS Statistics, version 23). Descriptive statistics will be used to summarize baseline characteristics, with continuous variables presented as mean ± standard deviation (SD) and categorical variables as frequencies and percentages. A p-value < 0.05 will be considered statistically significant, with a 95% confidence interval (CI). The Shapiro-Wilk test and graphical analysis will be used to assess whether the data are normally distributed. A repeated-measure ANOVA will be used to analyze group differences (intervention vs. control), changes over time, and the group-by-time interaction to assess treatment effects. Appropriate nonparametric tests, such as the Friedman test for within-group comparisons and the Mann–Whitney U test for between-group comparisons, will be employed if the assumptions required for parametric testing are not met. When appropriate, post hoc analyses will be carried out, and Type I error will be controlled using the Bonferroni correction. All randomized participants will be included in the analysis using an intention-to-treat (ITT) strategy, and missing data will be handled appropriately based on the last observation carried forward method.

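### The required 84, the anticipated 10% dropout and the planned 90 do not agree: 90 leaves 81 and allows for about 6.7% dropout (minor arithmetic inconsistency)

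*Protocol article*

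**What the plan says.** The Sample size calculation section of the protocol article reports that "42 subjects per group were shown to be necessary" for an effect size of 0.62, "an alpha level of 0.05" and a power of 0.8. It continues: "Hence, the total sample size was 84". The dropout step follows: "We anticipate a 10% dropout rate, so we will recruit 90 participants in total and allocate them equally between the two groups". The Abstract and the Study design section repeat 90, and Study design gives 45 per group.

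On the analysis set, the Data analysis section says: "All randomized participants will be included in the analysis using an intention-to-treat (ITT) strategy". Missing values are to be filled by last observation carried forward (LOCF).

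**The concern.** The sentence presents 90 as the consequence of needing 84 and expecting to lose 10%. A reader who checks it finds that 90 is too few by the usual calculation, and also by the cruder shortcut of adding 10%. The figure recurs elsewhere in the article, so it does not look like a typing slip, and nothing else in the article reconciles it.

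At stake is whether the trial, at the dropout rate it assumes itself, still meets its own target of 84 and the power attached to that target. The margin is thin, because 84 gives only just over 80%.

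**Working it through.** **Inputs**

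- From Sample size calculation: effect size 0.62, alpha 0.05, power 0.80, 42 per group, 84 in total, dropout 10%, recruitment 90.
- From Study design: 1:1 allocation, 45 per group.
- From Data analysis: all randomised participants analysed, with LOCF.
- Assumed, because the section names neither test nor sidedness: a two-sided two-sample t-test, with 0.62 read as Cohen's d.

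**1. Reproduce the base figure.** With the noncentral t distribution, d = 0.62, two-sided alpha 0.05 and power 0.80, n = 41.82 per group. This rounds up to 42 per group, 84 in total, with power 80.2%. A one-sided test would give 33 per group, so the two-sided test is the one that matches. The base figure is sound.

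**2. Dropout step.**

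- Needed to keep 84: N = 84/(1 − 0.10) = 93.3, so 94 (47 per group).
- Shortcut: 84 × 1.10 = 92.4, so 93.
- Left from 90: 90 × 0.90 = 81, which is 84 − 81 = 3 short.
- Dropout that 90 can absorb: (90 − 84)/90 = 6.7%.

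Neither rule gives 90.

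**3. Power if only completers count.** With 40 and 41 participants at d = 0.62, power is 78.7%. Against the nominal 80% that is a loss of 1.3 points. The effect detectable with 80% power rises from 0.619 (42 per group) to 0.630.

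**4. Power if all 90 are analysed.** A participant lost before the 4-week post-test has only a baseline value, so LOCF enters zero change. If a fraction f of each group does so, the mean difference becomes 0.62 × (1 − f). With the SD unchanged and 45 per group:

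| Share of the 10% lost before week 4 | f | Diluted d | Power |
|---|---|---|---|
| none (effect undiluted) | 0 | 0.620 | 82.9% |
| a quarter | 0.025 | 0.6045 | 80.9% |
| half | 0.05 | 0.589 | 78.9% |
| all | 0.10 | 0.558 | 74.5% |

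If all are lost early but the zeros also shrink the SD (control mean change taken as zero), the last figure is 78.0%. The split of dropouts before and after week 4 is an assumption throughout, because the protocol does not give it.

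**The case against.** The strongest reply is that the shortfall hardly matters. Lowering the assumed effect from 0.62 to 0.61 at 42 per group gives 78.9%, about the same loss, and no plan knows its effect that precisely. This stands, and it is why the point is minor. It does not make the three figures agree.

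A second reply is that the planned analysis includes all 90, so 81 is not the analysed number. This also stands. A reader might infer from the arithmetic that the trial cannot deliver its stated 80% power, or that LOCF certainly fails to restore it. The protocol supports neither reading. There is a follow-up visit after the 4-week post-test, and someone lost between the two carries a week-4 value, not zero change. At the week-4 comparison that person is not missing at all. The range of about 74% to 83% lies on both sides of 80%. Equally, the protocol does not show that LOCF rescues the figure, and its own dropout inflation treats dropouts as lost to the target.

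A third suggestion would be to keep 90 and claim that adjusting for baseline makes up the loss. The documents do not support that either. If 0.62 is in units of the final-score SD, power with 40 and 41 is about 82% at a baseline–outcome correlation of 0.3 and 89% at 0.5. If it is in units of the change-score SD, power is 92.8% at 0.3, 88.9% at 0.5 and 82.8% at 0.8. The section says the calculation rests on changes and gives no correlation, and the planned analysis is repeated-measures ANOVA. Such figures cannot serve as the justification.

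**Conclusion.** The sentence is wrong as written, and the error is confined to the dropout step. Ninety leaves 81 at 10% dropout, 94 would be needed to keep 84, and 90 corresponds to about 6.7% dropout. That part needs no assumption beyond the protocol's own figures.

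The effect on power is modest: about 1.3 points with 81 completers, or a range of about 74% to 83% under the planned analysis of all 90, depending on when dropouts leave. These power figures rest on the inferred two-sided t-test, which is not the planned repeated-measures ANOVA, and on the dilution assumptions set out above. This is a minor arithmetic inconsistency and no ground for judging the trial underpowered.

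**What to change.** Correct the one sentence in the Sample size calculation section and leave the recruitment figure as it is. Either of these statements is accurate:

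- 90 randomised participants allow for about 6.7% dropout while keeping 84; or
- 90 randomised participants with 10% dropout give 81 completers and about 79% power at an effect size of 0.62.

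The sentence should also name the test and its sidedness, so that 42 per group can be reproduced without inference. The cost is a slightly less favourable dropout allowance or power figure. No patients need to be added and the analysis need not change.

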### Eligibility criteria

The study's inclusion and exclusion criteria will be applied to participants through a screening process conducted by a diabetic foot surgeon and a consultant physiotherapist.

### Inclusion

Adults between 40 and 70 years old [24].Who have been diagnosed with Type-2 DPSN & Type-1 DPSN [31]Individuals who will give informed consent.The Michigan Diabetic Neuropathy Score (MDNS) is more than 6 [32].Symmetrical or asymmetric peripheral neuropathy accompanied by lower extremities discomfort lasting more than six months [32].

### Exclusion

Last six months, sciatica and radiculopathy of low back pain (lasting at least three days) [33].Musculoskeletal dysfunctions such as lumbar disc prolapses, scoliosis, and lumbar spine-related radiculopathy [34].Chemical, drug, or alcohol dependency.Medical diagnosis of a herniated disk in the lumbar spine [35].PregnancySurgery for back pain or any other type of surgeryAmputation of lower limb [36].

### Intervention

Participants will be randomly allocated to either the experimental group (neurodynamic mobilization) or the control group (sham neurodynamic mobilization). Both groups will additionally receive standard care consisting of transcutaneous electrical nerve stimulation (TENS) and a structured foot exercise program. All interventions will be delivered by trained physiotherapists following a standardized protocol to ensure consistency.

Experimental group (Neurodynamic Mobilization)

Participants in the experimental group will receive neurodynamic mobilization targeting the sciatic, tibial, sural, and common peroneal nerves.

General Treatment ParametersRepetitions:10 repetitions per set

Sets: 2–3 sets per session,

Hold time: 6–15 seconds per repetition.

Session duration: Approximately 30 minutes

Frequency: 3 sessions per week for 4 weeks.

Progression: The intensity and range of motion will be gradually increased based on the patient's tolerance and response to symptoms.

#### Sciatic nerve mobilization.

Position: The patient lies supine with pillows and maintains the therapist's proper position.

Technique: The ankle is positioned in dorsiflexion, and the therapist passively lifts the patient’s straight leg while keeping the knee fully extended (to increase tension on the nerve), and continues raising the leg until the patient feels tension or symptoms (e.g., pain, tingling). Once symptoms (such as pain or discomfort) appear, the therapist will lower the hip slightly to a pain-free position. Then, oscillatory mobilizations will be applied. The hip will be alternately moved between hip flexion (nerve loading) with ankle dorsiflexion (nerve loading) and hip extension (nerve unloading) with ankle plantarflexion (nerve unloading) [37–39].

#### Tibial nerve mobilization.

Position: The patient is in the supine position with pillows, and the therapist maintains proper position.

Technique: The therapist will place the ankle in dorsiflexion and eversion while the knee remains straight. The therapist then slowly moves the hip into flexion (lifting the leg) and the knee into extension to allow the nerve to glide smoothly. Once symptoms appear, the therapist will lower the hip slightly to a pain-free position. The hip will then be alternately flexed (nerve unloading) with ankle dorsiflexion and eversion (nerve loading) and extended (nerve loading) with ankle plantarflexion (nerve unloading) [37–39].

#### Common peroneal nerve mobilization.

Position: The patient lies supine with pillows and maintains the therapist's proper position.

Technique: The therapist will apply ankle plantarflexion and inversion, then passively flex the hip while keeping the knee extended. Once symptoms appear, the therapist will adjust the hip and knee to a pain-free position. The hip will be moved alternately in flexion of the hip joint (nerve unloading) with ankle plantarflexion and inversion (nerve loading) and then into extension (nerve loading) with a neutral ankle position (nerve unloading) [37–39].

#### Sural nerve mobilization.

Position: The patient lies supine with pillows and maintains the therapist's proper position.

Technique: The therapist will place the ankle and dorsiflexion and invert the ankle while passively flexing the hip, keeping the knee extended. Once symptoms appear, the therapist will adjust the hip and knee to a pain-free position, then alternately move into hip flexion (nerve unloading) with ankle dorsiflexion and inversion (nerve loading), and then into hip extension (nerve loading) with ankle dorsiflexion (nerve unloading) [37–39].

### Control group (Sham Neurodynamic Mobilization)

Participants in the control group will receive sham neurodynamic mobilization, in which similar movements are performed without applying nerve-tension techniques.

Position: The patient lies supine with pillows and maintains the therapist's proper position.

Technique: The therapist will place the patient's ankle in dorsiflexion and move the hip into abduction and flexion instead of true sciatic nerve-loading movements**.** The knee remains extended, and the therapist stops at a pain-free position**.** Each technique will be performed for 10 repetitions, with a hold time of a few seconds per repetition.

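### The sham is given its own, smaller stated dose, so handling within the component under test is not matched between arms

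*Protocol article*

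**What the plan says.** The Intervention section lists the treatment parameters under the experimental group: 10 repetitions in a set, "Sets: 2–3 sets per session", "Hold time: 6–15 seconds per repetition" and "Session duration: Approximately 30 minutes". Intensity and range progress with tolerance. Four nerves are treated (sciatic, tibial, common peroneal and sural), each with its own technique.

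The section Control group (Sham Neurodynamic Mobilization) does not refer back to those parameters. It sets its own: "Each technique will be performed for 10 repetitions, with a hold time of a few seconds per repetition". It describes a single movement and gives no sets, session length or progression.

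Other elements are common to both arms. Study design gives each arm 12 sessions in 4 weeks, and both receive TENS and the foot exercises. The Blinding section rests participant blinding on the two interventions being alike in structure.

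**The concern.** A sham should hold handling, contact and expectation constant, so that the difference between arms can be attributed to nerve tension. Here everything around the tested component is matched, while the component itself has two separately stated doses. If therapists follow the text, the experimental arm gets more handling as well as nerve tension.

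All the efficacy outcomes are open to this. VAS and Neuro-QoL are patient-reported. The primary outcome, MDNS, is described as vibration, light-touch and pinprick testing, which depends on the patient's response. The Discussion already expects a larger improvement in the experimental arm to show an added benefit of neurodynamic mobilization. With unequal handling, that reading is not secured.

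**Working it through.** **Inputs**

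| Element | Experimental (Intervention) | Sham (Control group) |
|---|---|---|
| Techniques | 4 | 1 described; the wording allows more than one |
| Repetitions | 10 per set | 10 per technique |
| Sets | 2–3; per nerve or per session not clear | not stated |
| Hold | 6–15 s | a few seconds, no number |
| Session time | about 30 min | not stated |
| Sessions | 12 | 12 |

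The plan gives no total dose to reproduce. Its session count is consistent: 3 per week × 4 weeks = 12.

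**Repetitions per session** (per leg, assuming the same legs are treated in both arms)

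- Experimental, sets counted per session: 2 × 10 = 20 to 3 × 10 = 30.
- Experimental, sets counted per nerve: 4 × 20 = 80 to 4 × 30 = 120.
- Sham, one movement: 1 × 10 = 10.
- Sham, one movement per nerve: 4 × 10 = 40.

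**Consistent pairings**

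- Sets per session against one sham movement: 20–30 vs 10, a ratio of 20/10 = 2 to 30/10 = 3.
- Four techniques in each arm: 80–120 vs 40, a ratio of 80/40 = 2 to 120/40 = 3.

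Over 12 sessions these become 240–360 vs 120, and 960–1,440 vs 480.

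Pairing sets per nerve with a single sham movement (80–120 vs 10) would give 8 to 12 times. It relies on the sham being only the one movement described, so I do not rest the point on it. Pairing 20–30 with 40 would give the sham more repetitions, but it counts the experimental sets across the session and the sham repetitions per technique. That mixes two readings.

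**Hold time, illustration only.** Assume that a few seconds means 2–5 s. With four techniques in each arm, the experimental hold runs from 80 × 6 = 480 s to 120 × 15 = 1,800 s, and the sham hold from 40 × 2 = 80 s to 40 × 5 = 200 s. The upper experimental figure is 30 minutes, which would fill the whole session before any movement time, so that corner is not realistic. The ranges do not overlap (480 s against 200 s at their closest), but the sham figures depend on the assumed 2–5 s and I claim no ratio from them.

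None of this enters the sample size calculation.

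**The case against.** The strongest reply is that silence is being read as a difference. The control-group section does not state a shorter session or a single set, the article condenses a fuller protocol, and it says that all treatment follows a standardized protocol. If the sham's 10 repetitions describe one set, and 2–3 sets were intended, the counts per technique agree at 20–30. It is true that session length is unstated. A reader might infer that sham sessions are shorter, and the document does not say so. But the control-group section is not merely silent. It fixes a repetition count and a hold, and agreement needs sets that it does not state.

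Second, a shorter hold may be a deliberate way of avoiding nerve tension. That stands, so the hold difference alone is not an error.

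Third, a reader might infer that blinding fails or that the document contradicts itself. Neither follows. Each patient sees only one arm, so a different number of sets does not by itself reveal allocation. Nothing says that the doses are equal, and likeness in structure can hold for the supine position and passive leg handling.

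Fourth, a reader might infer that the sham is itself a nerve-loading treatment. It puts the "ankle in dorsiflexion and move the hip into abduction and flexion instead of true sciatic nerve-loading movements", with the knee extended. The sciatic technique labels "hip flexion (nerve loading) with ankle dorsiflexion (nerve loading") and describes "keeping the knee fully extended (to increase tension on the nerve"). The labels do not settle this, because the tibial, common peroneal and sural techniques call hip flexion unloading, and the sural technique labels dorsiflexion as unloading in one phase. Nor do they support redesigning the sham with a flexed knee and neutral ankle. The phrase "with a neutral ankle position (nerve unloading") concerns the common peroneal nerve only, and such a sham would look less like the straight-leg technique and might weaken blinding.

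**Conclusion.** The point holds as a mismatch in stated dose. Followed as written, the plan gives the experimental arm 2–3 times the sham's repetitions per session on either of the two like-for-like readings. This rests on taking the control-group section at its word, with no unstated sets added, and on the same legs being treated in both arms.

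Unequal total contact time is a likely consequence, not a stated fact. A between-arm difference could partly reflect attention or expectation, but the documents give no means of computing how much. The point affects what the result can be attributed to. It does not affect the sample size, and it does not show that participants would be unblinded. It should be corrected because the correction is cheap and removes a competing explanation from outcomes that depend on the patient's response.

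**What to change.** In the control-group section, give the sham a session of about 30 minutes, one sham movement for each of the four nerve techniques, and the same sets and repetitions as the experimental arm. In the Intervention section, state whether the 2–3 sets are per nerve or per session. The hold may stay shorter if that is meant to avoid nerve tension. In that case say so, and keep total contact time equal.

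Study design has the last follow-up ending by August 2025. If treatment is complete, report the dose delivered in each arm (repetitions, sets, hold, minutes) and limit the attribution to nerve tension accordingly.

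The cost is a few lines of text, more therapist time per sham session, and possibly a slightly smaller contrast between arms.

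Separately, the sponsor should check that the sham's dorsiflexion with hip flexion and an extended knee is in fact non-loading. No redesign of the position is asked for here.

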#### Additional interventions for both groups.

***Foot Exercises:*** Both groups will perform foot exercises to improve mobility and sensory function. Exercises include: Foot tapping,

“V” shape making (foot movements creating a “V” shape),

Ankle rotations,

Tennis ball rolling (rolling a ball under the foot),

Foot somatosensory exercise (rolling a small ball under the foot for sensory stimulation)

Frequency:3–6 times per session for both feet**.** [40].

***Transcutaneous Electrical Nerve Stimulation (TENS):*** Both groups will receive TENS therapy

**Frequency:** 3 sessions per week for 4 weeks;

**Duration:** 20 minutes per session;

**Settings:** 80 Hz frequency, 150 µs pulse width

[41].

#### TENS electrode placement.

The placement of TENS electrodes depends on the target nerve being treated. Below are the recommended electrode placements for each nerve-

**Sciatic Nerve-** One electrode over the sciatic notch or gluteal area, near the piriformis muscle. Position the second electrode on the middle back of the thigh [42].

**Tibial Nerve-** One electrode just above the medial ankle (posterior to the medial malleolus). The second electrode on the calf, midway between the knee and ankle (posterior aspect) [43].

**Common Peroneal Nerve-** One electrode over the head of the fibula (just below the outer knee). And the second electrode along the lateral shin, midway between the knee and ankle [44].

**Sural Nerve-** One electrode over the mid-calf (posterior aspect, near the gastrocnemius muscle), the second electrode just above the lateral ankle (posterior to the lateral malleolus) [45–47].

#### Therapist training and standardization.

All interventions will be delivered by trained physiotherapists following a standardized protocol to ensure consistency across sessions.

### Outcome measures

**Socio-demographic Information:** The questionnaire will include socio-demographics such as patient ID, age, address, gender, occupation, education level, marital status, height, weight, BMI, etc.

**Primary outcomes**

The Michigan Diabetic Neuropathy Score (MDNS): It is a validated scoring system for the severity of diabetic peripheral neuropathy (DPN), which is measured by MDNS.

It comprises three sensory tests, totaling 46 points per limb. The Vibration Perception Threshold (VPT) is assessed using a 128 Hz tuning fork placed on the bony part of the big toe's joint to measure nerve response to vibrations. Light touch sensation is tested by applying a 10-gram monofilament on the top of the big toe, between the nail fold and joint. Pinprick sensation is evaluated using a standard pin on the top of the foot to check the response to sharp touch. These tests help assess the degree of nerve damage in individuals with DPN [48–50].

